## Abstract

**Background:**

An m-health application has been developed and implemented with community health workers to improve their counseling in a rural area of India. The ultimate aim was to generate demand and improve utilization of key maternal, neonatal, and child health services. The present study aims to assess the impact and cost-effectiveness of this project.

**Methods/design:**

A pre–post quasi-experimental design with a control group will be used to undertake difference in differences analysis for assessing the impact of intervention. The Annual Health Survey (2011) will provide pre-intervention data, and a household survey will be carried out to provide post-intervention data.

Two community development blocks where the intervention was introduced will be treated as intervention blocks while two controls blocks are selected after matching with intervention blocks on three indicators: average number of antenatal care checkups, percentage of women receiving three or more antenatal checkups, and percentage of institutional deliveries. Two categories of beneficiaries will be interviewed in both areas: women with a child between 29 days and 6 months and women with a child between 12 and 23 months. Propensity score matched samples from intervention and control areas in pre–post periods will be analyzed using the difference in differences method to estimate the impact of intervention in utilization of key services.

Bottom-up costing methods will be used to assess the cost of implementing intervention. A decision model will estimate long-term effects of improved health services utilization on mortality, morbidity, and disability. Cost-effectiveness will be assessed in terms of incremental cost per disability-adjusted life year averted and cost per unit increase in composite service coverage in intervention versus control groups.

**Conclusions:**

The study will generate significant evidence on impact of the m-health intervention for maternal, neonatal, and child services and on the cost of scaling up m-health technology for accredited social health activists in India.

## Introduction

Globally, maternal and child mortality is declining, although the pace of decline is not sufficient to attain Millennium Development Goals (MDGs) 4 and 5 in almost 128 out of 137 developing countries (1). Significant progress has been made in India for maternal and child health survival. The maternal mortality rate has decreased from 487 to 190 maternal deaths per 100,000 live births between 1990 and 2013 (2). In terms of child mortality, since 1990, the under-five mortality rate has decreased from 126 to 53 deaths per 1,000 live births during the same period (2). Nearly two-thirds of maternal and child deaths in India are contributed by a few states including Assam, Uttar Pradesh (UP), Uttarakhand, Rajasthan, Madhya Pradesh, Chhattisgarh, Bihar, Jharkhand, and Odisha (3). Not surprisingly, the coverage of key maternal, neonatal and child health (MNCH) services in these states is very low. For instance in UP, the coverage of institutional deliveries, full antenatal care (ANC), and full immunization were 45.6%, 29.6%, 45.3%, respectively, in 2011–12 (4).

Since the introduction of the National Rural Health Mission (NRHM) in India in 2005, a number of interventions have been introduced to bolster the coverage of services such as institutional delivery, immunization, and antenatal and postnatal care (5). While NRHM focused on the supply side through strengthening of the government health care system, it also initiated steps to generate demand through community mobilization by creation of a new cadre of community health workers called accredited social health activists (ASHAs) (5). ASHAs act as village-level grass roots workers to generate demand for services. Harnessed properly, this vast pool of human resources can be a potent asset in the Indian government health system. An evaluation of ASHAs in 2011 found that although a 23-day training schedule has been developed by the Ministry of Health and Family Welfare, the quality of training needs to be strengthened in order to improve the performance of ASHAs (6).

To supplement community health worker training and retention of knowledge, mobile technology has been considered an effective and sustainable method in developing countries (7). With the widespread use of mobile phones in the rural areas of India, reliable health information can easily be made accessible even to the remotest areas (8). Thus, built-in tools with health messages in the mobile phones can be used by the community health workers as an aid for counseling pregnant women and nursing mothers. A study conducted in rural areas of Tamil Nadu in India to assess the feasibility of text messaging in delivering maternal and child health care showed that mobile health messages were well perceived and accepted in the community (9). Knowledge about the recommended minimum number of ANC visits was reported to increase from 10 to 37% after women received text messages for health promotion on mobile phones (9).

Use of technology in the health sector, especially in rural areas that have significant health workforce deficiencies, has been endorsed by the government of India at the highest level (10). In this context, the ReMiND (Reducing Maternal and Neonatal Deaths) project was introduced in two blocks of the Kaushambi district in UP. As part of this project, a mobile health (m-health) application that runs on open source CommCare software has been introduced as a job aid for ASHAs. This m-health platform tracks and supports clients for the ASHAs and provides individualized service and counseling. It replaces paper registers and flip charts with open source software that runs on inexpensive phones. During home visits, it aids ASHAs to register clients and provides real-time guidance through key counseling points, decision support, and simple referral algorithms.

Similar m-health interventions in other countries have proven beneficial. For example, in Afghanistan m-health resulted in 20% improvement in antenatal attendance and a 22.3% improvement in the number of women receiving skilled deliveries at a health facility (11). In terms of quality of counseling (i.e. whether a client receives complete and accurate information), a study in India showed that after a period of 4 months of use of the CommCare application, frontline workers had increased their knowledge retention of at least three danger signs across all key health categories, from 48% at baseline to 70% (12).

A study reviewed all the controlled trials of m-health interventions between 1990 and 2010 to determine the effectiveness of m-health technologies in improving health care service delivery (13). The results highlighted that generally consistent finding of modest benefits associated with the use of mobile interventions by health care providers for diagnosis and management, so these interventions may be appropriate for implementation. The study showed that although much research has assessed the effectiveness of m-health, high-quality evidence is still lacking in the literature (13).

Another systematic review on the economic evaluation of m-health has shown that there is a lack of concrete evidence to fully assess the economic impact of telemedicine, e-health, and m-health systems (14). Deficiencies in design of studies, such as lack of randomized control trials, small sample sizes, and absence of quality data and appropriate measures further limit the relevance of findings. Furthermore, evaluations of such interventions in low- and middle-income countries are almost negligible, and there is no evidence from India or other Southeast Asian countries (14).

We therefore propose to undertake an impact assessment and a cost-effectiveness study to assess the incremental cost per disability-adjusted life year (DALY) averted and incremental cost per unit increase in composite coverage indicator with use of an m-health intervention delivered through ASHA workers for strengthening MNCH services compared with routine MNCH service delivery in one of the districts of UP in northern India.

## Background

### Study setting

The study will be conducted in the Kaushambi district in UP. Out of the district's eight community development blocks, the m-health intervention has been implemented in two blocks: Mooratganj and Manjhanpur.

The Catholic Relief Services (CRS) with the help of a local NGO, Vatsalya, introduced the CommCare m-health application to 259 ASHAs in the two intervention blocks in 2012. The ASHAs in the ReMiND project were provided with basic Java-based mobile phones operating on open source CommCare software (15). Extensive trainings of ASHAs were done in both blocks on the use of these phones. The ReMiND application has tailored content and guides the ASHA through the course of a woman's pregnancy and newborn child care. ASHAs use the application for the following purposes:To register each pregnant womanTo update her ANC record during home visits on the mobile applicationTo track her from pregnancy into the postpartum periodTo track the health of the newbornTo track the status of routine immunization until 2 years of ageTo provide appropriate counseling and support at each of these stepsThe phones contain locally relevant audio and visual prompts to help ASHAs navigate through the application. These recordings and pictures enrich the counseling experience of ASHAs during their home visits. The application uses the data entered about the pregnancy to guide ASHAs in providing timely and appropriate health information; it helps them to prioritize home visits; and it employs algorithms to assist in the early identification, treatment, and rapid referral to appropriate care of any danger signs among pregnant women or neonates (Fig. 1). While ASHAs have many tasks assigned to them, the key one is to identify pregnant women and visit them throughout the course of their pregnancy, seeing them through delivery in a safe facility and appropriate newborn care.

**Fig. 1 F0001:**
[figure not shown]
Conceptual frame work for impact of ReMiND project.

Data on services due and utilized by pregnant women, recorded by ASHAs through the m-health application, are pooled on a common server. The sector facilitators use the data to monitor all the ASHAs working in their area. These data are also shared with the health education officer at the primary health center level during monthly meetings. Thus, CRS works in coordination with the health system to monitor the performance of ASHAs using data generated by the m-health application (Fig. 1).

### Theory of change

The state of UP is one of the major contributors in total maternal and child deaths in India with low coverage of key MNCH services (3). Kaushambi is one of the 19 high focus districts in UP and exhibits some of the worst health statistics with maternal mortality ratio and infant mortality rate being 366 per 100,000 live births and 80 deaths per 1,000 live births, respectively (16, 17), which are higher in comparison with both national and state averages (4, 18). The district has a population of 1.2 million and a female literacy rate of 48.6% (19). An important reason for the lack of utilization of MNCH services is the reduced demand for services. This can be corroborated based on findings from Coverage Evaluation Survey which report that among pregnant women who do not seek ANC care, 55% do not consider it necessary. Similarly, 28% of women who deliver at home in UP did not consider it necessary to deliver in a health facility (20). This signifies a potential to increase utilization through demand generation.

One of the ways to generate demand is through quality counseling of women during pregnancy. Previous assessments of ASHA performance found them wanting in terms of their skills to counsel women effectively (21). Use of m-health with its associated audio–visual support is considered as a means for improving the quality of counseling services delivered through ASHAs. Improved knowledge about the need for services, together with an enabling environment with support from ASHAs, was likely to drive demand and hence utilization of MNCH services. Apart from this, continuous monitoring and supervision of ASHA performance through generation of real-time data on utilization of MNCH services as a result of the m-health application is also likely to contribute toward increased coverage of the preventive service. The m-health intervention includes five modules that could help ASHAs to track pregnant mothers in the village and ensure adequate ANC, postnatal care, newborn care, and immunizations through 2 years of age, which leads to the demand for MNCH services in the community finally leading to an increase in coverage of these services.

Increase in coverage of preventive services is likely to result in reduction of morbidities during pregnancy, child-birth, and neonatal period. Reduction in morbidity will in turn contribute to reduced mortality. The intervention is also likely to improve the care seeking during an episode of illness. Improved care seeking is likely to have an impact on mortality as a result of reduced case-fatality rates with treatment as compared with no treatment. Finally, the contact with public health services through the medium of ASHA workers may also change patterns of care seeking, that is, public versus private sector utilization of care. This is likely to affect the cost of health care services through reduction in out-of-pocket (OOP) expenditures and an increase in health system costs for provision of care. This is likely to have a bearing on the overall cost-effectiveness of intervention (Fig. 1) (22).

## Objectives

First, the primary objective of the present study is to assess the impact of the m-health application in the ReMiND project for ASHA workers on utilization of MNCH service coverage. Second, we aim to assess the cost-effectiveness of this m-health intervention in terms of incremental cost per DALY averted for delivering the intervention, as compared with routine services. Cost-effectiveness will also be assessed in terms of incremental cost per unit increase in composite service coverage indicator. Finally, we will assess the cost of scale-up for the m-health application, as it is implemented in the ReMiND project, at district and state level in India.

## Methodology

Impact assessment of the m-health intervention is provided in detail below.

### Overview of study design

The study has been approved by the Institute Ethics Committee of the Post Graduate Institute of Medical Education and Research, Chandigarh, India. Written informed consent will be obtained from all study participants. Administrative approval will be obtained for collection of relevant data.

We will use a quasi-experimental design comprising pre- and post-intervention observations with a control to assess the impact of the ReMiND project. Data from the Annual Household Survey (AHS) undertaken by the Registrar General of India in district Kaushambi in 2011 will be used for baseline or pre-intervention assessment (4). The AHS is the largest demographic survey in the world and covers two and a half times that of the Sample Registration System (India's most regular source of demographic statistics). The sampling design adopted for the AHS is a uni-stage stratified simple random sample without replacement, except in case of larger villages in rural areas (i.e. having a population greater than or equal to 2000 as per 2001 census), wherein a two-stage stratified sampling procedure has been applied. The details of the AHS survey are incorporated in the supplementary material.

We will undertake a cost-effectiveness analysis household (CEAHH) survey in 2015 in two intervention blocks and two control blocks from the Kaushambi district to assess the coverage of various MNCH services that represent the post-intervention status. To carry out the CEAHH survey, two structured interview schedules were developed after an extensive review of existing tools used in AHS, the National Family Health Survey, the District Level Household Survey, and the Coverage Evaluation Survey.

Together, the AHS and the CEAHH will be used to assess the impact of the ReMiND m-health intervention using a difference in differences (DID) analysis. To reduce selection bias, before DID is performed, propensity score matching (PSM) will be used to match the cases from the intervention blocks with those in the control group based on their socio-demographic characteristics, for the period between 2011 and 2015 (4). Further, subgroup analysis will be done to analyze the impact of intervention among various levels of underlying factors, such as the mother's education and the occupation of the head of household.

### Study area

The study area for the CEAHH survey will be two intervention and two control blocks out of a total of eight community development blocks in the Kaushambi district. The two control blocks will be selected based on matching for three health service utilization indicators: average number of ANC checkups, percentage of women receiving three or more ANC checkups and percentage of institutional deliveries.

### Sampling

The primary sampling unit (PSU) for the CEAHH survey will be a village. For selection of PSUs, a list of all villages from the two intervention and two control blocks will be prepared. From all villages in Kaushambi, 10% of each will be selected from the intervention area and the control area. This means that 69 PSUs each will be selected randomly from the intervention and control areas, using the probability proportional to size method.

In each PSU, a household enumeration will be undertaken to identify all mothers with a child in the age group of 29 days to 6 months, or between 12 and 23 months on the date of the survey. This list will serve as the sampling framework to randomly select the required number of mothers in each category for interview. The number of clients to be interviewed per PSU will again be selected by the probability proportional to size method and will be determined based on the relative size of the PSU.

The clients (mothers with a child in the 29 days to 6-month or 12- to 23-month age range) within each PSU will be selected using systematic random sampling. If more than one child in the respective age category is present in a given household (i.e. more than one child is between 29 days and 6 months or more than one child is between 12 and 23 months), then one will be randomly selected. If the family has one child in the 29 days- to 6-month range and one in the 12- to 23-month range, then both children would be part of the sampling frame and would have the same probability of being selected as would any other child in the sampling frame.

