Additionally, mothers in both categories will be interviewed in the intervention and control area about the extent and quality of services offered by the ASHAs during the antenatal and postnatal home visits. Specific questions will be posed to mothers in the intervention area to assess the usage of the mobile application and their satisfaction with this mobile-assisted counseling.

### 
Data analysis

DID will be the primary analysis and will be based on the AHS and CEAHH data from intervention and control areas. Propensity scores will be used to match the women of intervention area with control area based on their socio-demographic characteristics. This will help to reduce the selection bias by taking into account the variation caused by known confounders. The AHS dataset for analysis comprises a total of 450 women: 225 from the intervention areas and 225 from the control areas. The CEAHH data have 1,053 women with a child aged 1–6 months each in intervention and control area. Similarly, a total of 1,391 women with a child aged 12–23 months in intervention and control area are part of the CEAHH dataset.

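### Village size enters both sampling stages of the CEAHH survey, so the sample is not self-weighting and can bias coverage and cost levels, and to a lesser extent the DID, unless design weights are used

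*Protocol article*

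**What the plan says.** The rule is in the protocol article under Sampling. At the first stage, "69 PSUs each will be selected randomly from the intervention and control areas, using the probability proportional to size method". At the second stage, "The number of clients to be interviewed per PSU will again be selected by the probability proportional to size method", and that number "will be determined based on the relative size of the PSU". Mothers "within each PSU will be selected using systematic random sampling", from a list made by enumerating households in that village.

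The same section says that a child in a family with children in both age groups "would have the same probability of being selected as would any other child in the sampling frame". The frame meant there is the list compiled in each village.

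The baseline comes from another survey with another design. Under Overview of study design: "The sampling design adopted for the AHS is a uni-stage stratified simple random sample without replacement, except in case of larger villages", where sampling is in two stages. Under Data analysis: "DID will be the primary analysis and will be based on the AHS and CEAHH data from intervention and control areas". The only weighting described for the impact estimate is by the propensity score. The article names no survey weights and does not say that the analysis will be unweighted.

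**The concern.** Two standard two-stage designs give every woman the same chance of selection: PPS selection of villages with a fixed take in each, or equal-probability selection of villages with a take proportional to size. The Sampling section combines the size-dependent half of each. Women in large villages are then over-represented.

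If service use varies with village size, for example because larger villages lie closer to facilities, unweighted CEAHH levels describe a population tilted towards large villages. Three uses of the data are exposed:

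- the 2015 coverage levels and the composite coverage indicator;
- the utilization and out-of-pocket inputs to the cost model, where no differencing removes a level error;
- the DID, to the extent that the distortion differs between areas, that design differences from the AHS do not cancel, or that the intervention effect itself varies with village size.

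The propensity score does not replace design weights. Its named examples (literacy, caste, occupation, age) do not include village size.

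**Working it through.** **The plan's own figures.** Two-sided alpha 0.05, 80% power, a 5-point difference and unpooled variance, from Sample size: n = (1.96 + 0.842)² × [p1(1−p1) + p2(1−p2)] / 0.05².

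- Morbidity, 18.9% v 23.9%: 7.849 × (0.1533 + 0.1819) / 0.0025 = 1,053.
- Full immunization, 30.8% v 35.8%: 7.849 × (0.2131 + 0.2298) / 0.0025 = 1,391.

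Both stated sizes reproduce with no inflation factor, so they hold no allowance for unequal weights.

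**Inclusion probability.** Let village i have size M_i and let M be the total for the area.

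- Stage 1: 69 × M_i / M, capped at 1.
- Stage 2: take n_i = c × M_i, so the within-village fraction is c × M_i / M_i = c, a constant.
- Overall: 69 × c × M_i / M, proportional to M_i until a village is selected with certainty.

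Below that cap, a woman in a village four times as large is four times as likely to be interviewed. This step needs no outside data. It takes the size measure to be proportional to the number of eligible women.

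**Size of the level error (assumptions).** Sizes are lognormal, coverage is linear in log2(size), and villages are drawn by PPS without replacement. The number of villages per area is not stated. If 69 is 10% of all villages in the district, there are about 690. Two of eight blocks would then hold about 172 if blocks are similar in size. If the 10% applies within each area, each area has about 690. The error is the shift in mean log2(size) between sample and population, multiplied by the slope.

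| Villages per area | CV | Shift (doublings) | Error at 3 points per doubling | Error at 5 points per doubling |
|---|---|---|---|---|
| 172 | 0.5 | 0.29 | 0.9 | 1.5 |
| 172 | 0.8 | 0.47 | 1.4 | 2.4 |
| 172 | 1.0 | 0.53 | 1.6 | 2.7 |
| 690 | 0.5 | 0.32 | 1.0 | 1.6 |
| 690 | 0.8 | 0.69 | 2.1 | 3.5 |
| 690 | 1.0 | 0.95 | 2.8 | 4.7 |

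At a slope of 0 the error is 0 throughout.

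**Comparison of designs.** Simulation with 345 villages, CV 0.8, slope 3 and 1,053 women. Bias in coverage was +2.0 points for PPS with proportional take, unweighted. It was 0.0 for the same design with inverse-probability weights, for PPS with fixed take, and for simple random villages with proportional take.

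**Effect on the DID.** Same set-up, difference in 2015 bias between the two areas: 0.1 point with slopes 3 v 3, 1.4 points with 3 v 1, and 2.0 points with 3 v 0.

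**Price of weighting.** With few certainty selections the Kish effect is about 1 + CV²: 1.25 at CV 0.5 and 2.0 at CV 1.0. With 172 villages, certainty selection lowers it to 1.22-1.49.

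**Fixed take.** 1,053 / 69 = 15.3 and 1,391 / 69 = 20.2 mothers per village.

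**The case against.** A reader might infer that CEAHH coverage is biased and cannot be compared with the AHS. The documents do not support that. Bias needs coverage to vary with village size, and no data on this are given. It also needs an unweighted analysis, which the article does not announce. Unequal inclusion probabilities are legitimate when weighted, and weights are a detail that an article may leave to the full protocol or analysis plan. Two surveys with different designs can be compared if each is properly weighted.

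The primary estimand is the DID. Both areas lie in one district, are sampled by one rule, and have blocks matched on utilization, so much of any level error should cancel. Setting a level error against the 5-point target would overstate the threat.

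The simple 1 + CV² formula also overstates the tilt when many villages are drawn. It says that the average sampled woman's village is 25%, 64% and 100% larger than that of the average woman at CV 0.5, 0.8 and 1.0. With 172 villages per area and certainty selection, the figures are 21%, 31% and 32%.

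Finally, a fixed take may not be reachable everywhere. The article's 1.2 million people over about 690 villages gives about 1,740 per village. At an assumed 25-30 births per 1,000 and a five-month window, that is about 18-22 eligible younger-group mothers. Under the same lognormal assumptions, about 15-29% of selected villages would then have fewer than 15.

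All of this stands as a limit on the consequence and on the remedy. It leaves the allocation rule untouched: the rule is stated, uses size twice, and is not self-weighting. The equal-probability sentence about children works within a village list and does not equalise chances across villages.

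**Conclusion.** The point holds as a defect of the stated sampling rule. That the sample is not self-weighting follows from the text alone. The consequence is conditional: without design weights, CEAHH levels can be off by about 0.9-4.7 points under the assumptions above, and by nothing if outcomes do not vary with village size. The DID error is smaller, about 0.1 point with equal slopes and 1.4-2.0 points if the size-coverage slope differs between areas as assumed. These DID figures do not cover design differences from the AHS that fail to cancel, or effects that vary with village size, because the documents give nothing from which to size them. The point deserves correction because the remedy is cheap and the cost inputs gain nothing from differencing.

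**What to change.** Keep PPS selection of villages and take a fixed number per village, about 15 younger-group and 20 older-group mothers, wherever that many are eligible. Where fewer are eligible, interview all of them. If fieldwork has been done, leave the sample as it is.

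In every case, record for each village the size measure, the first-stage probability, the enumerated number of eligible mothers and the number interviewed. Weight each woman by the inverse of the product of the two stage probabilities. Use these weights, with AHS design weights at baseline, in the matched DID and in the coverage and cost inputs, and say so in the Data analysis section.

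The enumeration already planned in each village supplies the second-stage counts, so the extra work is small. The cost is precision. If the size-related take is kept, the weighting design effect is about 1.2-2.0, so 1,053 women carry the information of about 878 to 527 (1,053 / 1.2 and 1,053 / 2.0), and 1,391 that of about 1,159 to 696. With a mostly fixed take the loss is small.
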